## Abstract

**Background:**

Currently, there is limited evidence to guide intervention and service delivery coordination for youth who suffer a concussion and subsequently experience persistent post-concussive symptoms (PCS) (Lumba-Brown et al. JAMA Pediatr 172(11):e182853, 2018; Lumba-Brown A et al. JAMA Pediatr 172(11):e182847, 2018). We have developed a collaborative care intervention with embedded cognitive-behavioral therapy, care management, and stepped-up psychotropic medication consultation to address persistent PCS and related psychological comorbidities. The CARE4PCS-II study was designed to assess whether adolescents with persistent symptoms after sports-related concussion will demonstrate better outcomes when receiving this collaborative care intervention compared to a usual care (control) condition.

**Methods/design:**

This investigation is a randomized comparative effectiveness trial to receive intervention (collaborative care) or control (usual care). Two hundred sports-injured male and female adolescents aged 11–18 years with three or more post-concussive symptoms that persist for at least 1 month but less than 9 months after injury will be recruited and randomized into the study. The trial focuses on the effects of the intervention on post-concussive, depressive, and anxiety symptoms measured 3, 6, and 12 months after baseline.

**Discussion:**

The CARE4PCS II study is a large comparative effectiveness trial targeting symptomatic improvements in sports injured adolescents after concussion. The study is unique in its adaptation of the collaborative care model to a broad spectrum of primary care, sports medicine, and school settings. The investigation incorporates novel elements such as the delivery of CBT through HIPAA complaint video conferenceing technology and has excellent widespread dissemination potential should effectiveness be demonstrated.

**Trial registration:**

ClinicalTrials.gov, NCT03034720. Registered on January 27, 2017.

**Electronic supplementary material:**

The online version of this article (10.1186/s13063-019-3662-3) contains supplementary material, which is available to authorized users.

## Background

Sports-related concussions are endemic among children and adolescents and constitute a major public health challenge, particularly when they fail to resolve in a timely manner. Estimates of sports-related concussions in youth range from 1.1 to 1.9 million per year in the United States [3]. While symptoms from sports-related concussion normally resolve spontaneously within days to weeks following injury, an estimated 14% or more of school-aged children experience significant morbidity that lasts for several months [4]. Persistent post-concussive headache, fatigue, dizziness, and inattention confer marked functional impairment for affected youth and can significantly interfere with academic performance and social functioning [5, 6]. Psychological symptoms, including depression and anxiety, commonly accompany post-concussive symptoms (PCS) [7]. Symptoms of depression correlate with other post-concussion symptoms [8] and may further prolong recovery from primary symptoms, as has been demonstrated in patients with traumatic brain injury [7, 9–12]. Furthermore, recommended activity and school restrictions may contribute to increases in depression and anxiety [13]. Taken together, the complexities of persistent PCS in conjunction with co-morbid psychological symptoms create a significant burden for the injured youth, their families, and schools.

Currently, there is limited evidence to guide intervention and service delivery coordination for sports concussion-exposed youth [1, 2, 14–16]. Current clinical paradigms for persistent PCS emphasize education about symptoms, anticipatory guidance around return to physical and cognitive activity, and reassurance of a full recovery [17]. While these guidelines are adequate for patients with typical recovery, providers of patients who experience chronic symptoms are left with few treatment options because the evidence base for treatment of youth with persistent PCS is lacking [18]. Psychotherapy and medication management services can be difficult to access and are not incorporated into the standard of care [19]. Thus, healthcare providers face a major challenge in managing patients with persistent post-concussive symptomatology.

Collaborative care has demonstrated effectiveness in treating chronic disorders where both physical and psychological symptoms are present, and may be well-suited to address service delivery coordination among sports injured youth. Collaborative care is a healthcare delivery model that integrates medical and mental health and allows for individuals to receive care that is titrated to align with their clinical needs. Large-scale randomized clinical trials have established the effectiveness of collaborative care interventions that combine care management, evidence-based pharmacotherapy, and CBT in treating adult primary care patients with depressive, anxiety, and post-traumatic stress disorders [20–23]. Other studies have documented the effectiveness of collaborative care interventions in reducing anxiety symptoms and improving functional impairments in injured adults after acute injury [24–26]. A series of investigations have now established the feasibility and effectiveness of the circumscribed delivery of collaborative care for pediatric patients in primary care settings [27–30]. Fewer investigations have successfully targeted anxiety and depressive symptoms in acutely injured youth [31]. Given the constellation of somatic, cognitive, and emotional impairments associated with persistent PCS, an integrated approach to symptom management which targets these impairments in combination holds promise for youth [32–35].

We have developed a collaborative care intervention with embedded cognitive-behavioral therapy (CBT), care management, and stepped-up psychotropic medication consultation to address persistent PCS. Our pilot data showed that this intervention had large, clinically meaningful effects on reducing persistent PCS and increasing quality of life for adolescents compared to usual care [36]. Collaborative care interventions may be optimal for youth suffering from PCS presentations as these models can facilitate linkages across primary care pediatric, rehabilitation, specialty, and school-based service delivery sectors.

CBT is a robust evidenced-based treatment for psychiatric disorders including depression and anxiety; an emerging literature also supports CBT as an efficacious intervention for PCS [36, 37]. Cognitive-behavioral therapy has shown response rates of 60–80% among youth aged 12–17 years with depression and among youth aged 7–17 years with anxiety disorders, with long-term outcomes equivalent to anti-depressant medication [38–40]. Across injured and other trauma-exposed populations, CBT is the evidence-based treatment modality for anxiety most consistently recommended by best-practice treatment guidelines [41–44]. CBT has also been successfully delivered by phone and video conferencing [32, 36]. Initial studies suggest that CBT intervention strategies can reduce persistent traumatic brain injury (TBI) symptoms, including memory impairment, difficulties with concentration, and somatic symptoms such as fatigue, sleep problems, and irritability [45].

An emerging evidence base suggests that pharmacological interventions may be an effective adjunctive tool in combination with psychotherapeutic interventions in the management of PCS, anxiety, and depressive symptoms in youth and adults [39, 46–53]. The selective serotonin reuptake inhibitor (SSRI) and serotonin norepinephrine reuptake inhibitor classes of anti-depressant medication can be delivered safely to adolescents and young adults suffering from anxiety and depression with appropriate psychiatric oversight [31, 46]. Post-injury pharmacotherapy can target non-specific persistent TBI symptoms such as insomnia [25, 26, 31]. Some, but not all, investigations suggest that post-concussive headaches may be effectively targeted with pharmacotherapy [54].

Intervention models that bridge primary care, community, and specialty care services in order to deliver evidence-based treatments are a crucial element of the integration of healthcare after sports injury in youth [1, 55] (Fig. 1). Intervention models that serve to link acutely exposed youth to evidence-based treatments have not been widely implemented and represent a crucial next step in adolescent sports injury intervention development [55]. The aim of this manuscript is to describe the protocol for the CARE4PCS II study in Seattle, WA, USA.

**Fig. 1 Fig1:**
[figure not shown]
CARE4PCS-II Collaborative Care Intervention model

### Objectives and hypothesis

This study was designed to assess whether adolescents with persistent symptoms after sports-related concussion will demonstrate better outcomes when receiving a collaborative care intervention compared to usual care (control) condition. Four main aims are addressed; first, we want to compare the groups with respect to post-concussive, anxiety, and depressive symptoms at 3, 6, and 12 months follow-up. Second, we seek to examine the effectiveness of the intervention in improving function and health-related quality of life among adolescents with persistent symptoms after sports-related concussion. Third, the study will also evaluate the impact of the collaborative care intervention on school performance. Finally, we aim to explore the heterogeneity of treatment effects in outcomes by examining the interaction of the treatment effect with group membership in distinct subgroups of the population.

We hypothesize that adolescents who receive the collaborative care intervention will demonstrate clinically and statistically significant reductions in PCS and depressive and anxiety symptoms over the course of the 12-month study compared to the usual care control group. We also hypothesize that adolescents who receive collaborative care will exhibit a clinically meaningful improvement in functioning and health-related quality life compared to the usual care control group. For the third aim, we expect that adolescents who receive the collaborative care intervention will receive individualized treatment and community resource linkages which will improve their school performance and return to full activities at school compared to usual care. Finally, we anticipate that three distinct subgroups will emerge from the study population—adolescents who recover from symptoms, adolescents with chronic psychosocial problems, and adolescents whose symptoms wax and wane over time—and these groups will have heterogeneity in treatment effects.

## Methods/design

### Design

This investigation is a randomized comparative effectiveness trial allocated in a 1:1 ratio to receive intervention (collaborative care) or control (usual care). The trial focuses on the effects of the intervention on youth outcomes 3, 6, and 12 months after baseline. Figure 1 shows the intervention model and Fig. 2 shows recruitment and flow of participants through the study.

**Fig. 2 Fig2:**
[figure not shown]
Consort trial flow diagram

### Trial setting

Subjects will be recruited from geographically dispersed primary care medical pediatric clinics, sports medicine specialty clinics, pediatric neurology clinics, and rehabilitation medicine clinics throughout the Seattle, Puget Sound and the Western Washington area of the USA.

### Participants and procedures

#### Eligibility criteria

Two hundred sports-injured male and female adolescents aged 11–18 years with at least three PCS that persist for at least 1 month but less than 9 months after injury will be recruited and randomized into the study if they and a parent can read and speak in English. The diagnosis of concussion will be made by a qualified medical provider. Adolescents with prior concussions will not be excluded. There will be active recruitment by weekly scanning of the appointment lists for the Sports Medicine, Neurology, Neurosurgery, and Rehabilitation Medicine clinics at Seattle Children’s Hospital main campus and four satellite locations, and the Sports Medicine and Rehabilitation Medicine clinics at Harborview Medical Center. Some of these settings serve patients from surrounding states, who will also be eligible for this trial.

Adolescents who have suffered spinal cord or other severe injuries that prevent participation will be excluded from the study. Adolescents will also be excluded if they have had a diagnosis of schizophrenia or psychosis, or present with active and acute suicidal ideation. Parents of adolescents who report concerns about their child’s ability to communicate may be excluded from the study pending consultation with principal investigators.

#### Informed consent

All study procedures were approved by the Seattle Children’s Hospital institutional review board (IRB; protocol number STUDY00000437) prior to the initation of participant recruitment.The research assistant or study coordinator will give each parent a brief overview of the study and ask the potential parent participant whether or not they would be interested in hearing a more detailed description and learning if their child might be eligible. If the potential parent participant wants to learn more, they will be asked to complete a brief eligibility screening tool. If the adolescent meets eligibility criteria and the parent still wants to learn more about the study, the research assistant or study coordinator will give a copy of the consent form to the parent and review the entire form with them, allowing participants to ask questions or voice concerns. The recruitment procedure will also include discussion of payment for study participation over the course of the year after the injury. Parent participants will also prospectively consent to the release of school records. After parent consent, the eligible adolescent will go through a similar study assent procedure.

There is minimal risk to subjects from data collection procedures, but the small risks that are present include the potential for distress, invasion of privacy, an accidental breach of confidentiality, and the inconvenience of participating. Significant risks to the health of subjects are low, given that the intent of the study is to compare usual care with an enhancement of usual care that is expected to be effective and safe. Upon enrollment, parent and adolescent participants will be given a study information sheet with the study follow-up survey timeline and phone number. All subjects will be in contact by phone with the study research assistants, and intervention subjects will be in frequent contact with their study care manager. Participants will be asked to notify the study personnel if any difficulties arise.

### Randomization

Randomization will occur in a 1:1 ratio, in blocks of four to six patients, according to a computer-generated random assignment sequence prepared by the study biostatistician. Once generated, intervention and control group assignments will be entered into a password-protected tracking system with access limited to study coordinator, care manager, and principal investigator. Randomization will be conducted by the study coordinator. After randomization occurs a letter and email will be sent to the referring provider and participant family to notify them as to which group the participant has been randomly assigned.

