#### Masking of treatment allocation

Study group assignments will be kept in sequentially numbered opaque envelopes that will be opened by unblinded study staff after baseline assessments to ensure allocation concealment of the randomization group. Research assistants conducting all baseline assessments and follow-up interviews will be blinded to block sizes and remain blinded to study group assignment throughout the study. Since the study team includes both unblinded (principal investigators, study coordinator, care managers) and blinded (research assistants) staff, unblinding of the research assistants is not ever necessary, although it could inadvertently occur through participant disclosure.

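### As written, the tracking-system access rule leaves upcoming allocations unconcealed from the study coordinator and principal investigator, and it does not fit with the envelope procedure

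*Protocol article*

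**What the plan says.** Four sections of the protocol article bear on the point.

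- **Randomization.** The study biostatistician prepares a computer-generated 1:1 sequence in blocks of four to six. The next sentence says that, after generation, the "assignments will be entered into a password-protected tracking system with access limited to study coordinator, care manager, and principal investigator". It is followed by this statement: "Randomization will be conducted by the study coordinator".
- **Informed consent.** First contact is shared between two roles: "The research assistant or study coordinator will give each parent a brief overview of the study". The parent then completes a short eligibility screen, after which "the research assistant or study coordinator will give a copy of the consent form to the parent" and goes through it with them.
- **Eligibility criteria.** Where there is concern about the child's ability to communicate, families "may be excluded from the study pending consultation with principal investigators".
- **Masking of treatment allocation.** Here the article describes a second mechanism: "Study group assignments will be kept in sequentially numbered opaque envelopes that will be opened by unblinded study staff after baseline assessments", and this is given as the means of concealment. The section lists the principal investigators, study coordinator and care managers as unblinded. Research assistants are blinded to assignment and to block sizes.

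No section says how the tracking system and the envelopes work together, or that assignments not yet revealed are hidden from the coordinator or the investigators.

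**The concern.** Allocation concealment requires that nobody who can affect whether or when a patient enters knows the next assignment. The Randomization section gives access to two roles that can have such influence. The coordinator may make the first approach, conduct consent and then randomize. The principal investigator is consulted on a discretionary exclusion. If either can look up the next assignment, the timing of an approach, the effort put into consent, or a borderline exclusion can depend on it, even unintentionally.

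This could unbalance prognosis between the arms at entry. The Data analysis section plans to adjust for baseline variables that differ significantly between groups. That helps with measured prognosis but cannot be relied on for unmeasured prognosis. The trial is powered for a modest effect, d = 0.36, so even a small imbalance would matter in relation to it.

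**Working it through.** The protocol gives no figure for concealment, so there is none to reproduce. The main check sets the sections side by side.

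| Role | May approach or consent families | Part in exclusions | Conducts randomization | Access to assignments in tracking system |
|---|---|---|---|---|
| Research assistant | Yes | None stated | No | No (blinded) |
| Study coordinator | Yes | None stated beyond the screening process | Yes | Yes |
| Principal investigator | None stated | Consulted on one discretionary exclusion | No | Yes |
| Care manager | None stated | None stated | No | Yes |

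**Step 1: what is entered, and when.** The sentence on the tracking system opens with a reference to generation and follows directly on the sentence about the computer-generated sequence. The natural reading is that the whole list is entered when it is produced, before participants are enrolled.

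**Step 2: what the envelopes add.** An envelope opened after baseline hides an assignment only from people who cannot see it elsewhere. For the coordinator and principal investigator, on the reading in step 1, it hides nothing. For research assistants it still does.

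**Step 3: predictability, as an illustration.** Suppose a person cannot read the list but knows past assignments and the block size (assumed fixed, and either 4 or 6). In a 1:1 permuted block of size 2b, the expected share of assignments known with certainty is 1/(b + 1).

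- Blocks of 4: b = 2, so 1/3 = 33.3%. Check: up to swapping the arms, the sequences are AABB (2 certain), ABAB (1) and ABBA (1); the mean is 4/3, and (4/3)/4 = 33.3%.
- Blocks of 6: b = 3, so 1/4 = 25.0%.
- Enumerating all blocks, the best guess is right 70.8% (blocks of 4) or 68.3% (blocks of 6) of the time.

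A person who can read the list knows every upcoming assignment. The 33.3% and 25.0% would be lower if block sizes were mixed and unknown to that person. The protocol blinds only the research assistants to block sizes and does not say whether the coordinator knows them.

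**Step 4: scale of a shift, as an illustration.** Let the assumed prognostic difference between arms be s, in SD units, and compare it with the planned d = 0.36 from the Power analysis section.

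- s = 0.05: 0.05/0.36 = 14%
- s = 0.10: 0.10/0.36 = 28%
- s = 0.15: 0.15/0.36 = 42%

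The values of s are assumptions with no basis in the document. The planned effect is a group-by-time interaction with baseline as one of four assessments, so a shift in baseline severity would not carry over one for one.

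**The case against.** The strongest reply is that the tracking system may hold only assignments already revealed. The three roles with access are the same ones listed as unblinded, and they need revealed assignments to run the trial. Care managers have no described part in recruitment and begin work after randomization, so their access fits a record of past allocations. On that reading the envelopes hold future assignments, the system holds past ones, and nothing conflicts. A condensed article might also leave the link between the two tools to the full protocol.

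This reading is possible, and if it is the practice the access concern disappears. But the text does not state it, and it is the less natural reading of the sentence. Nor is this only a missing detail: the article states an access rule that, followed as written, would undo the concealment it claims elsewhere.

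Other parts of the reply stand and limit the point:

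- Research assistants may also do the consenting; they are blinded and have no access. A reader might infer that allocation is concealed from nobody. The document does not support that.
- A reader might infer that the investigator decides all exclusions. The stated role is consultation on one of them.
- The envelopes are described as opaque and numbered; the article does not say whether they are sealed, and nothing here turns on it.
- Properly run envelopes are an accepted method, so a new electronic system is not required.

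**Conclusion.** The point holds as a conflict in the text with a real risk attached. On the plain reading, upcoming allocations are not concealed from the study coordinator and the principal investigator, and the Randomization and Masking sections describe procedures that do not fit together. The conclusion rests on the assumption that the sequence is entered when generated, which the wording suggests but does not settle.

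A reader might go further and infer that enrolment was biased, or that all assignments were in fact known in advance. The documents support neither: they describe access, not its use, and the full-knowledge figure depends on the plain reading being the practice. The risk cannot be sized from the document. The percentages for predictability and for the prognostic shift are illustrations under stated assumptions. The planned sample size and power calculations are not affected.

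**What to change.** 1. Describe one mechanism in both sections: either the existing envelopes or a restricted electronic release.
2. State that the unrevealed sequence is held only by the biostatistician, or by someone else with no role in recruitment or eligibility.
3. Release each assignment only after consent, eligibility (including any investigator consultation) and baseline assessment are complete.
4. Limit tracking-system access for the coordinator, care manager and principal investigator to assignments already revealed.
5. For participants already randomized, state whether unrevealed assignments were viewable, by which roles, and report any access records that exist. The Data and Safety Monitoring Board already reviews threats to internal validity and could receive this.

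The cost is a short amendment and a change in who holds the list; no participants are added. If only revealed assignments were ever entered, one sentence saying so is enough. Recruitment began in March 2017 and was expected to finish near the end of March 2019, while the protocol version is dated October 2018. Items 1 to 4 may therefore protect few remaining participants, and item 5 matters most for interpreting the results.
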